### Measures

Demographic (e.g., parental age, parental job, and parental educational level), neonatal (e.g., gestational age, birth weight, and Apgar score), and clinical variables (e.g., NICU length of stay and minor morbidities) will be obtained from medical charts. Parent-report questionnaires are summarized and described in Table 2. As for behavioral coding purposes, the videotapes obtained from two cameras during the lab FFSF procedure will be edited offline using Movavi Video Suite 2020 software and a single synced video showing both frontal views of the caregiver and the infant’s face, hands, and torso will be produced. Videos will be micro-analytically coded for infants’ and caregivers’ target interactive behaviors according to an adaptation of the Parent–Infant Coding Scheme (PICS, Version 4.0; Brambilla et al., 2023) as reported in Table 2. PICS codes will be computed as a percentage of time for each FFSF episode (Table 3).

**Table 2 tab2:** Details of questionnaires included in the study.

Construct	Questionnaire	Reference	Item N	Likert scale	Description	Study wave(s)
Parental NICU-related stress	Parental Stressor Scale—NICU (PSS-NICU)	Miles et al. (1993)	46	5-point	Three main factor scores representing stress related to infants’ appearance, environmental sights and sounds, and parental role alteration	T1 (only VPT)
Sensory profile	Sensory Profile-2 (SP-2)	Dunn (2014)	54	5-point	The infant version (0–6 months) identifies 5 sensory patterns. The toddler version (7–35 months) identifies four sensory patterns.	T2, T3, T4
Anxiety symptoms	State–Trait Anxiety Inventory (STAI-Y)	Spielberger et al. (1983)	40	4-point	One trait score representing a tendency to feel anxiety and one state score representing the present levels of anxiety	T2, T4
Depression symptoms	Beck Depression Inventory (BDI-II)	Beck et al. (1996)	21	4-point	Global score representing a quantitative appreciation of the severity of symptoms of depression	T2, T4
Parenting stress	Parenting Stress Index—Short Form (PSI-SF)	Abidin et al. (2006)	36	5-point	Three subscale scores addressing parental distress, parent–child dysfunctional interaction, and stress related to difficult child behavior. A global score is also obtained.	T2, T3, T4
Temperament	Infant Behavior Questionnaire-Revised (IBQ-R) very short form	Gartstein and Rothbart (2003)	37	7-point	Three subscale factor scores addressing negative affectivity, surgency, and regulatory capacity.	T2, T3, T4

VPT, very preterm; NICU, neonatal intensive care unit.

**Table 3 tab3:** Selection of codes from the Parent-Infant Coding Scheme (PICS, Version 4.0).

Variable	Levels	Description
A. Both interactive partners		
Emotional state	Negative	Clear display of negative emotionality (e.g., eyes, mouth, general movements of the face or the body, and other vocal or non-vocal signals) including fussing and crying.
	Neutral	No clear display of negative or positive emotionality.
	Positive	Clear display of positive emotionality (e.g., eyes, mouth, general movements of the face or the body, and other vocal or non-vocal signals) including smiles and laughs.
Gaze direction	Face-directed	Attention focus is on the interactive partner’s face
	Object-directed	Attention focus is on the interactive partner body (e.g., hands and torso) or other objects.
	Avoiding	The subject is actively avoiding eye contact as displayed by head and body movements/posture.
Approach/withdrawal	Withdrawal	Evident leaning backward and/or turning the head away to avoid interaction
	Neutral	No evident backward or forward movements.
	Approach	Evident leaning forward and/or reaching forward to engage in interactive behaviors.
B. Parental-specific codes		
Vocal inputs	No voice	No vocal productions.
	Negative	Vocal comments that convey explicit critique or rejection of infants’ behaviors or state.
	Pragmatic	Vocal comments that are finalized to modify or instruct the interactive partner’s cognitive state, such as requests, attention-getting, and explanations.
	Social	Vocal comments that convey playful and social engagement such as singing, laughing, and playing nursery rhymes.
	Nurturing	Vocal comments that express appreciation or acceptance of infants’ behaviors or state or are finalized to soothe infants’ stress. These also include mind-related comments (e.g., “you think” and “you want”) and mirroring of infants’ communicative bids.
Tactile inputs	No touch	No tactile stimulations.
	Negative	Tactile stimulations that clearly appear intrusive and/or provoke or increase a negative emotionality state in the interactive partner.
	Pragmatic	Tactile stimulations that are finalized to modify or instruct the interactive partner postures or movements in the environment, such as holding, shadowing, and attention-getting.
	Social	Tactile stimulations that convey playful and social engagement such as tickling, squeezing, and any other appropriate entertaining tactile stimulations that are fast-paced, dynamic, repetitive, and/or characterized by quick cinematic features.
	Nurturing	Tactile stimulations that are finalized to soothe or regulate the behavioral state of the interactive partners. These include stroking, kissing, massaging, and any other appropriate tactile stimulations with clear regulatory functions and conveying a sense of affective closeness.

The complete coding manual is available upon request to the corresponding author.

### Plan of EEG data elaboration

#### Pre-processing pipeline

Dyadic EEG data will be pre-processed with a fully automated pipeline built using the MATLAB-based (The MathWorks Inc., 2024) interacting toolbox EEGLAB (Delorme and Makeig, 2004). A brief description of the main pre-processing steps is available in Figure 2.

**Figure 2 fig2:**
[figure not shown]
Study design. NICU, neonatal intensive care unit; VF, video-feedback intervention; CU, care as usual; CA, corrected age.

The parent and infant signals will be pre-processed separately with the same steps and parameters for both. First, data filtering will be performed with the application of a bandpass 1–30 Hz filter as the planned analyses (see below) will be conducted on the lower (theta and alpha) frequency bands. Subsequently, flat and outlier channels will be detected using the Neonatal EEG Artifact Removal (NEAR) plugin (Kumaravel et al., 2022) and retained (i.e., put in a separate temporary matrix) for later interpolation. Dyads in which at least one of the members displays a signal with more than 15% (*N* > 5) of flagged channels will be excluded from further analyses. The EEG signal from all non-flagged channels will undergo noise correction through the artifact subspace reconstruction (ASR; Chang et al., 2020), with burst criterion (k) set at 10; subsequently, analysis of the components of the signal will be performed through the independent component analysis (ICA; runica function with default settings), producing as many components as the number of good channels. The resulting components will be then classified through the ICLabel (Pion-Tonachini et al., 2019) plugin. Every component flagged as having a 50% or more probability of being an ocular artifact will be rejected. At this stage, the matrix containing the flat and outlier channels will be re-merged with the EEG matrix, and the bad channels will be interpolated through spherical interpolation using the pre-processed signal. The signal will be then re-referenced to the average signal of the channels and split into three different sets containing each phase of the experimental procedure (Play, Still-Face, and Reunion): Each of these sets will be subsequently segmented into 1,000 ms epochs avoiding overlaps. Bad data segments containing residual artifacts in each of the three phases will be identified. All segments in which at least one of the target channels used for estimates of dyadic co-regulation (see below) displays a voltage exceeding ±150 μV (Debnath et al., 2020) will be marked as rejected. The rejected epochs in the infant’s and parent’s signals will be merged to obtain the final pool of rejected epochs for the dyad. This ensures that all the rejected epochs for one interactive member of the dyad will be similarly mirrored for the other partner. Dyadic data will undergo further analyses if their signal contains at least 30 good epochs in both the Play and Reunion phases; if this criterion is not met, their signal will undergo manual epoch rejection performed by an expert EEG coder. In case after the manual epoch rejection, the dyad will result having less than 30 good merged epochs in at least one of the FFSF episodes, the signal will be excluded from further analyses.

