#### FFSF procedure

At 9 months (CA for VPT participants), mothers and infants will take part in a FFSF procedure in the laboratory. The FFSF will include three episodes: During the Play episode (2 min), mothers and infants will interact face-to-face avoiding the use of toys and pacifier; during the Still-Face episode (1 min), mothers will be asked to interrupt any communication toward the infant, to maintain a still, poker face, while maintaining eye-contact; and during the Reunion episode (2 min), unconstrained interaction will be resumed. The procedure has been previously adopted to assess biobehavioral dimensions (Provenzi et al., 2019; Provenzi et al., 2017) and physiological underpinnings (Montirosso et al., 2010; Mantis et al., 2014) of socio-emotional stress regulation in VPT infants. The entire procedure will be videotaped for the offline coding of specific maternal and infant interactive behaviors (see *Measures* for details).

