### Statistical power and sample size estimates

The sample size has been estimated according to over-arching Aim 2, setting parameters as follows: medium effect size, *f* = 0.25, *alpha* = 0.05, *beta* = 0.20, number of groups = 3 (VPT-VF, VPT-CU, and FT). The procedure yielded a total sample size of 159 subjects (53 subjects per RCT arm). Nonetheless, considering the longitudinal nature of the study and the attrition rate related to EEG tasks with infants, an oversampling of *n* = 80 (~ +50%) subjects per RCT arm was planned to secure the minimum sample size for appropriately powered statistical analyses.

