### Sources of bias and mitigation strategies

The heterogeneity of VPT infants’ conditions should not be underestimated. Even in the absence of severe comorbidities and brain injuries, the experience of NICU hospitalization might be very different for each infant and their parents. To avoid extreme variations, the gestational age range will be constrained between 28 and 35 weeks. Moreover, stress related to the NICU environment will be evaluated and quantified with a well-validated questionnaire (Miles et al., 1993). Selection issues might affect random allocation plans in RCT arms. The allocation to VPT-VF and VPT-CU arms will occur by using an automatically generated list of binary codes that will be consecutively matched with the enrolled families across consecutive sampling. This will reduce the risk of self-selection. To further avoid confounding by infant sex and assure sex distribution balancing, the random allocation will be stratified by infant sex by *post-hoc* controls every 20 enrollments. Parental gender will also be unconstrained, inviting the primary caregiver—and not explicitly the mother—to participate in the study, VF intervention, and observational procedures. EEG procedural steps and artifacts might easily result in the loss of subjects in a longitudinal study; a 50% oversampling was planned to achieve the minimum sample size for adequately powered statistical analyses.

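### The two steps of the 30-epoch rule count different phases, and the second discards a dyad's usable phases along with the failing one

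*Protocol article*

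**What the plan says.** The Pre-processing pipeline section cuts each phase of the 9-month Face-to-Face Still-Face (FFSF) recording into non-overlapping one-second epochs. An epoch rejected in either partner is rejected for the dyad. Retention is then decided in steps:

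- Automated step: "Dyadic data will undergo further analyses if their signal contains at least 30 good epochs in both the Play and Reunion phases".
- Manual step: "if this criterion is not met, their signal will undergo manual epoch rejection performed by an expert EEG coder".
- Final step, after manual review: a dyad is removed if it has "less than 30 good merged epochs in at least one of the FFSF episodes, the signal will be excluded from further analyses".

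The FFSF procedure section gives Play and Reunion 2 minutes each and Still-Face 1 minute ("during the Still-Face episode (1 min" is its wording).

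Oversampling is the provision stated for EEG loss. The sample size section says "The procedure yielded a total sample size of 159 subjects (53 subjects per RCT arm" and that "an oversampling of *n* = 80 (~ +50%) subjects per RCT arm was planned". The section on sources of bias repeats that "a 50% oversampling was planned to achieve the minimum sample size for adequately powered statistical analyses". No loss rate by phase or by arm is given. For Specific aim 2 the article plans separate ANOVAs of the co-regulation indices across the three groups.

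**The concern.** The automated step names two phases; the final step covers all three. Still-Face quality therefore plays no part for a dyad that passes the automated step, but can remove a dyad that did not. Two dyads with the same Still-Face recording can be treated in opposite ways.

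The final step also acts on the whole signal. A dyad with ample clean Reunion data is lost from every analysis because Play, or Still-Face, stayed below 30. A minimum epoch count is a legitimate quality rule. Applying it to the dyad instead of to the phase is what costs data.

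In the two randomised groups, video-feedback (VF) and care as usual (CU), this exclusion takes place after allocation and depends on what happened in the outcome session. The intervention addresses infant emotion and state regulation. If poorly regulated infants yield fewer clean epochs, retention could differ by arm. Oversampling can restore numbers, but it cannot restore comparability of the arms.

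**Working it through.** **1. The plan's own sample size.** Inputs from the sample size section: f = 0.25, alpha 0.05, power 0.80, three groups. For a one-way ANOVA with noncentrality f² × N and 2 and N − 3 degrees of freedom, N = 156 gives power 0.797 and N = 159 gives 0.805. The smallest multiple of 3 that reaches 0.80 is 159, or 53 per arm, so the stated figure reproduces. 53 × 1.5 = 79.5, rounded up to 80. The allowance for loss from all causes is (80 − 53)/80 = 27/80 = 33.75%.

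**2. The threshold as a share of each phase.** Play or Reunion: 120 s gives at most 120 epochs, and 30/120 = 25%. Still-Face: 60 s gives at most 60 epochs, and 30/60 = 50%. Epochs must be clean in both partners.

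**3. The steps side by side, read literally.**

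| Automated result: Play and Reunion | After manual review | Outcome |
|---|---|---|
| Both ≥ 30, Still-Face < 30 | Not sent | Dyad kept |
| One < 30 | Play and Reunion now ≥ 30, Still-Face < 30 | Whole dyad excluded |
| One < 30 | That phase still < 30, the others ≥ 30 | Whole dyad excluded |
| One < 30 | All three ≥ 30 | Dyad kept |

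Rows 1 and 2 show the inconsistency. Rows 2 and 3 show usable phases being discarded.

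**4. Size of the loss.** Every excluded dyad must first have failed Play or Reunion. Let q be the failure rate in each of those two phases (assumed, since the article gives none), with phases independent, no other attrition and no rescue by manual review. Retention is then at least (1 − q)².

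- Failure rate that uses up the allowance: 1 − √(53/80) = 1 − √0.6625 = 1 − 0.814 = 18.6%.
- q = 15%: 80 × 0.85² = 57.8, about 58 per arm (power 0.84 if all three groups lose equally).
- q = 20%: 80 × 0.80² = 51.2, about 51 per arm (power 0.79).
- For comparison, analysing one phase on its own data: 80 × 0.85 = 68 (power 0.90) and 80 × 0.80 = 64 (power 0.88).

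**5. Possible bias.** This simulation is illustrative and every input is assumed. The true effect is 0.50 SD. A latent distress score drives epoch failure, with correlation 0.5 between phases. The control pass rate is 80% or 90% per phase. VF lowers distress by 0.3 or 0.5 SD, and distress correlates −0.3 or −0.5 with the index.

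- Play and Reunion both required: estimated effect 0.433 to 0.481 SD. Retention (CU against VF) is about 83% against 88–91% at the 90% pass rate, and about 69% against 76–81% at the 80% pass rate.
- One phase used on its own data: 0.455 to 0.488 SD.
- Distress unrelated to the index, or not differing by arm: about 0.50 SD under either rule.

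**The case against.** The strongest reply is that this is a stated, ordinary quality rule with a manual rescue step, and that EEG loss was foreseen and oversampled for. Artifact correction comes before epoch rejection, the voltage limit applies only to target channels, and loss can come from the parent's signal as well as the infant's. Imputation, weighting and exclusion tables are commonly left to an analysis plan or full protocol, which is not shown here. Much of this stands. A minimum epoch count is appropriate, and the absence of such tables or methods is not the finding.

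Two stronger readings are tempting and not supported.

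- A reader might infer that any single phase below 30 drops the dyad, so that the stressful one-minute Still-Face decides who is analysed. On the literal text a Still-Face shortfall alone does not drop a dyad, because the automated step does not name that phase. Figures that require all three phases (12.8% failure uses up the allowance; 49 or 41 per arm left at 15% or 20%) therefore overstate the loss.
- A reader might infer that the rule is known to select on infant distress. The article nowhere links distress to rejected epochs, and the intervention's stated aim is regulation. Bias would require that distress drives exclusion, differs by arm and relates to the index.

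The reply does not answer the mismatch between the two steps or the loss of adequate phases. Oversampling addresses power only.

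**Conclusion.** The point holds as a defect in a stated rule. Its two steps count different phases, and its final step removes whole dyads where removing a phase would do. The mismatch and the whole-dyad exclusion follow from the text alone.

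The size depends on assumed failure rates. About 18.6% failure in each of Play and Reunion would exhaust the 80-to-53 allowance. That allowance must also cover dropout to 9 months and the separate exclusion for flagged channels. Positive correlation between phases or successful manual review would reduce the loss. Selection by arm is plausible but unproven. Under the assumed settings it moves a 0.50 SD effect to roughly 0.43–0.48, a modest attenuation. This should be changed, but it does not undermine the trial.

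**What to change.** 1. Reconcile the two sentences so that the same phases count at the automated and the final step.
2. Apply the 30-epoch threshold phase by phase: set only the failing phase to missing and keep the dyad's other phases.
3. Analyse the indices in a mixed model with phase as a repeated factor, so that dyads with some phases missing still contribute.
4. Report exclusions by arm and phase.
5. Add one sensitivity analysis for missing EEG outcomes (multiple imputation or inverse-probability weighting) using the T1–T3 data already collected.

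No new data are needed. The cost is more than wording, because the mixed model would replace the separate ANOVAs stated for Specific aim 2. Phases will contribute unequal numbers, and the model relies on a missing-at-random assumption. Some sparse Still-Face recordings that the literal text now keeps would be set to missing. Phase-wise exclusion reduces possible selection without removing it, which is why the reporting and the sensitivity analysis belong with it.

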
#### Estimating indices of inter-brain co-regulation

Several inter-brain synchronization indices have been proposed so far to estimate the coupling between two brains (Czeszumski et al., 2020). Since there is still debate on the appropriateness of each inter-brain synchronization measure, we plan to compute and compare several indices (see Table 4). To further check for spurious findings and gather stronger evidence that the obtained co-regulation estimations are not artifact production, we will compare the synchronization indices obtained from the real dyads to surrogate data generated by randomly pairing mothers and infants from different dyads.

**Table 4 tab4:** Indices of inter-brain co-regulation adopted in the 2-BRAINED study.

Index	Description	Notes	Reference
Phase-Locking Value (PLV)	Frequency-specific transients of phase locking independent of amplitude. The value ranges from 0 to 1: values closer to 0 indicate random signals with unsynchronized phases; values closer to 1 indicate stronger coupling between the two signals.	While previous studies focused mainly on infant frequency bands, cross-frequency PLV indices will be obtained for the purposes of the 2-BRAINED study.	Lachaux et al. (1999); Canolty and Knight (2010)
Imaginary Coherence (ICoh)	Computed through spectral density (power) of each participant and cross-spectral density between them to estimate the average phase difference and consistency of phase difference synchronization.	ICoh is expressed as a complex number: the real part represents how much the coherence is driven by instantaneous interactions; the imaginary part shows how much the coherence is based on lagged interactions.	Dikker et al. (2021); Turk et al. (2022)
Amplitude-Amplitude Coupling (AAC)	Expressed as Pearson’s correlation coefficient between normalized power time courses of the two signals.	Amplitude coupling was suggested as a valid alternative to phase coupling for three main reasons: amplitude changes are more easily estimated; amplitude modulations are more extensively characterized across EEG studies; amplitude modulations are more sensitive to neural coupling phenomena non-detectable with other phase-related measures.	Haresign et al. (2022); Koul et al. (2023)

The computation of synchronization measures will preferentially occur considering homologous channels for the sake of interpretability and computational costs. However, as an exploratory analysis, we will also compute synchronization between non-homologous channels because we can hypothesize that synchronization tasks between mother and infant can involve different brain areas in the two actors (Endevelt-Shapira et al., 2021).

Regarding the frequency bands on which the synchronization measures will be computed, we will mainly consider alpha and theta. Indeed, these frequencies have been found to be involved in parent–infant social tasks, with theta fluctuations linked to changes in shared attention during joint play of parent and infant (Wass et al., 2018), enhancement of alpha and theta power linked to changes in directed gaze (Leong et al., 2017), and fluctuations in alpha band linked to changes in emotional states of mother and child (Santamaria et al., 2020).

Moreover, since we are interested in the dynamic evolution of brain-to-brain synchronization, we plan to evaluate the trend of each synchronization index over time (i.e., over the epochs). In particular, we are interested in the change between an asynchronous to a synchronous state, which is defined as reparation. Reparation is a dyadic process in which unmatched dyadic states are transformed into matched dyadic states. We will compute the rate and the latency of reparation considering the EEG synchronization indices as previously performed in synchronized behaviors assessment (Provenzi et al., 2015).

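### Re-pairing mothers and infants across dyads tests synchrony against chance and common procedure, but cannot separate neural coupling from artifact shared within one dyad

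*Protocol article*

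**What the plan says.** The section *Estimating indices of inter-brain co-regulation* lists three indices (PLV, imaginary coherence and amplitude-amplitude coupling). It then adds a further check, meant to "gather stronger evidence that the obtained co-regulation estimations are not artifact production". The check compares the real-dyad indices with "surrogate data generated by randomly pairing mothers and infants from different dyads". No other type of surrogate is stated. For imaginary coherence, Table 4 explains that "the imaginary part shows how much the coherence is based on lagged interactions", but gives that index no role in controlling artifact. *General and specific aims* makes PLV the primary measure.

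The cleaning steps are in *Pre-processing pipeline*:
- "The parent and infant signals will be pre-processed separately with the same steps and parameters for both".
- Signals receive "noise correction through the artifact subspace reconstruction" with k = 10.
- After ICA, "Every component flagged as having a 50% or more probability of being an ocular artifact will be rejected". No rejection rule is stated for muscle or movement components.
- Data are "subsequently segmented into 1,000 ms epochs avoiding overlaps". Epochs exceeding ±150 μV on a target channel are rejected, and a rejection in one partner is mirrored in the other.

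Physical contact is part of the recorded interaction. The behaviour codes in Table 3 include "Tactile stimulations that convey playful and social engagement such as tickling, squeezing", as well as holding and stroking. Table 1 makes caregivers' affective touch one of the intervention's topics.

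**The concern.** A surrogate comparison tests only against what the surrogates preserve. A mother and an infant from different sessions share neither neural coupling nor anything else particular to one live session: a tickle that moves both caps, a joint postural shift, a disturbance in the room. An excess of real over surrogate is therefore expected if there is coupling, and equally if there is only artifact shared within the dyad. The plan offers the check as evidence against artifact, and against this kind it supplies none.

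Such artifact can survive the cleaning. Each partner is cleaned separately, so no step looks for a disturbance present in both at once. Only ocular components are rejected, and movement or muscle activity that ASR does not correct and that stays below the voltage limit remains in the data.

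What is at stake is how the PLV results are interpreted. If video-feedback changes how much mothers touch their infants, contact artifact could differ between VPT-VF and VPT-CU and appear as a PLV difference. The surrogate check would not flag it. Randomization does not remove it, because touch would be a consequence of treatment.

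**Working it through.** **The plan's own figures.** The article gives no figure for this check. The simulations borrow 53 dyads from the sample-size section (53 per arm, 159 in total). That total reproduces for a one-way ANOVA with three groups and f = 0.25: the minimum is 158, or 159 with equal groups (power 0.805). It has no further bearing here.

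**Step 1: what each comparison contains.** Per epoch, PLV = |mean over time of exp(i(φ_mother − φ_infant))|, averaged over epochs. A real pair is (mother d, infant d); a surrogate is (mother d, infant d′) with d′ ≠ d.

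| Source of phase locking | In real pairs | In surrogates | Adds to real minus surrogate |
|---|---|---|---|
| Chance and finite-epoch bias | yes | yes | no |
| Artifact or timing common to all dyads | yes | yes | no |
| Neural coupling in one dyad | yes | no | yes |
| Artifact shared at one moment in one dyad | yes | no | yes |

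The last two rows are identical, so the comparison cannot tell them apart.

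**Step 2: size.** Background signals were independent between partners. A shared component of the same amplitude as the background was added to both partners in a fraction of epochs. Real and re-paired dyads were compared with a one-sided paired t-test at 0.05.
- Setting A: 60 one-second epochs, 4–7 Hz, 150 replicates.
- Setting B: 120 one-second epochs (the 2-minute Play episode), 3–6 Hz, 60 replicates.

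The article states none of the contamination rate, amplitude, lag, band limits or form of test; all are assumptions. Entries are the share of runs that pass with **no neural coupling** and zero-lag artifact.

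| Epochs contaminated | PLV, A | PLV, B | AAC, B | ICoh, B |
|---|---|---|---|---|
| 0% | 4% | 3% | 7% | 7% |
| 5% | 29% | 38% | 98% | 7% |
| 10% | 72% | 85% | 100% | 3% |
| 20% | – | 100% | 100% | 7% |
| 25% | 100% | – | – | – |

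Imaginary coherence passed in 1% to 5% of runs in A. Monte Carlo error at a true 5% with 60 replicates is √(0.05 × 0.95 / 60) = 0.028, so the uncontaminated rates fit a calibrated test.

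The PLV excess in B grows roughly in proportion to the contaminated share:
- 5%: 0.460 − 0.455 = 0.005
- 10%: 0.465 − 0.455 = 0.010
- 20%: 0.475 − 0.453 = 0.022

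**Step 3: variants in setting B, all at 20% of epochs.**
- True zero-lag coupling of the same size: PLV 0.475 against 0.454, passes 100%. The simulated signal is the same as the artifact, so this only illustrates the point.
- Artifact reaching the second partner 40 ms later: PLV, AAC and imaginary coherence all pass 100%.
- Artifact with the same waveform and timing in all dyads: PLV 0.477 against 0.477, passes 7%.
- Amplitude changes locked to the common procedure: AAC 0.523 against 0.523, passes 2%.

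The check does its job in the last two cases, and imaginary coherence fails to protect in the second.

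**Step 4: reach into the aims.** Aims 1 and 2 compare groups; they do not compare real with surrogate dyads. Equal contamination in all groups would cancel in expectation. If one arm had 5% and another 10%, mean PLV in setting B would differ by 0.465 − 0.460 = 0.005 with no coupling in either. The article gives no standard deviation for PLV, so this cannot be put on the scale of f.

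**The case against.** The strongest reply is that the article presents the comparison as an additional check on top of a full cleaning pipeline. It speaks of stronger evidence, not proof, and states no decision rule. It applies the comparison to all the indices, so imaginary coherence against its own surrogates is already implied. The pass rates also depend on assumed contamination, and the simulations do not model what ASR, the voltage limit and mirrored rejection would leave behind. All of this stands, and it limits the size of the point. It does not restore the check's stated purpose: against artifact shared within a dyad, the PLV comparison adds no evidence at any contamination rate.

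The documents do not support four stronger readings that a reader might infer:
- *Re-pairing removes every shared artifact.* Artifact common to all dyads survives re-pairing, and the check guards against it.
- *The check passes whenever the synchrony is artifactual.* That depends on enough contaminated epochs: at 5%, PLV passed in only 29% to 38% of runs.
- *Imaginary coherence can settle the matter.* It resists zero-lag artifact, but the 40 ms variant passed every time. Nothing in the article shows that contact reaches two bodies and two caps without lag.
- *Aims 1 and 2 are already biased.* They are affected only if shared artifact differs by group. That is plausible for Aim 2 but not demonstrated.

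A neural response to a partner's voice is also not recording artifact. Voice belongs in the sensitivity analysis as a common input, not as an error to be removed.

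**Conclusion.** The concern holds in this limited form. Random re-pairing rules out chance, finite-epoch bias and procedure-driven synchrony. A real-over-surrogate excess in PLV does not show that the estimate is free of artifact shared by a mother and her own infant at the same moment. With no coupling and 5% to 25% of epochs contaminated at zero lag and signal-level amplitude, PLV passed in about 29% to 100% of runs. The inability to separate the two sources follows from how the surrogates are built and needs no assumption. The pass rates rest on assumed contamination, amplitude and lag. Bias in the group comparisons needs the further condition that artifact differs by group. The wording and the analysis should be changed before the data are analysed, but the design need not change.

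**What to change.** 1. State that re-pairing rules out chance and common procedure-driven synchrony only, and limit the conclusion to that.
2. Add a sensitivity analysis of PLV, and of the group comparison, that accounts for touch and voice. Restrict to epochs coded as having neither touch nor voice where enough remain; otherwise adjust for the percentage of time in touch and in voice. The plan's own minimum of 30 good epochs is a natural threshold. It would need 30 / 120 = 25% of a 2-minute Play episode to be both clean and free of touch and voice.
3. Read the imaginary part of coherence against its surrogates as supporting evidence against zero-lag artifact, not as proof. Report a PLV excess without an imaginary-coherence excess as not separable from shared artifact or zero-lag common input.

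Cost: no new data. The article summarises the behaviour codes as percentages of each episode, so aligning them to one-second epochs takes extra work, and few epochs may remain. The touch and voice codes cover the parent only, so infant crying and movement stay in. Touch and voice may be consequences of treatment, so the restricted or adjusted result can only be a sensitivity analysis. Imaginary coherence also discards genuine zero-lag coupling, which makes that reading conservative.
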